## Abstract

**Background:**

The first line of pharmacological treatment for severe depressive disorders in young people is selective serotonin reuptake inhibitors (SSRIs). However, beneficial clinical effects are rarely observed before several weeks into treatment. Nitrous oxide (N_2_O) has a long-standing safety record for pain relief and has been used in adults and young people. In adults with severe treatment-resistant depression, a single dose of N_2_O had significant antidepressant effects, with maximum antidepressant effects observed 24 h after administration. However, the antidepressant effects of N_2_O have never been investigated in adolescents with a confirmed diagnosis of depression in a prospective trial. The aims of this study are to (1) investigate whether a single inhaled N_2_O administration leads to antidepressant effects in adolescents with depression at 24 h, (2) determine whether combined N_2_O and SSRI administration (commenced after N_2_O intervention) provides a clinically significant improvement in mood over and above the benefits from SSRI administration alone, and, (3) investigate whether the effect seen following N_2_O administration can be used as a predictor of SSRI treatment response.

**Methods/design:**

In this study, we will use a single-blind, randomised, placebo-controlled design. Patients aged between 12 and 17 years with major depressive disorder will be recruited. This study will consist of two phases: phase A and phase B. During phase A, participants will be randomised to receive either inhaled N_2_O or placebo (air) for 1 h. In phase B, participants will receive open-label pharmacological treatment with the SSRI fluoxetine and will be followed over a 12-week period. Participants will undertake mood assessments at 2 and 24 h after N_2_O or placebo administration (phase A) and weekly during the 12-week follow up in phase B.

**Discussion:**

We expect an antidepressant effect from a single dose of inhaled N_2_O compared with placebo at 24 h after administration. Additionally, we expect that subjects treated with N_2_O will also show greater improvements than the placebo group after 6 and 12 weeks into fluoxetine treatment because of potential additive antidepressant effects. Such findings would be of clinical importance because currently children and adolescents often do not experience any symptom alleviation for several weeks following the initiation of SSRIs.

**Trial registration:**

Australian and New Zealand Clinical Trials Registry, ACTRN12616001568404. Registered on 14 November 2016.

**Electronic supplementary material:**

The online version of this article (doi:10.1186/s13063-017-2342-4) contains supplementary material, which is available to authorized users.

## Background

One in 16 young Australians is currently experiencing depressive symptoms, which underlines the significant prevalence of depressive disorders in minors [1]. Approximately 6.3% of Australians aged between 16 and 24 years have experienced an affective disorder in the last 12 months [1]. Selective serotonin reuptake inhibitors (SSRIs) are frequently used for the pharmacological treatment of depressive disorders. SSRIs are amongst the most frequently prescribed antidepressants and are known to increase the availability of the neurotransmitter serotonin (5-HT) in the brain, which is thought to contribute to their antidepressant effects. However, the complete mechanism of action of SSRIs is still not fully understood. In particular, the question why antidepressant effects are often observed only after a delay of several weeks into treatment, despite the fact that single doses of SSRI administration can lead to significant changes in activation of brain regions that are known to be associated with mood and emotion regulation (i.e., the amygdala, hippocampus and prefrontal cortex) [2]. The described delay in the onset of antidepressant effects after SSRI administration can put young patients at risk for exacerbation of low mood and other associated depressive symptoms, such as self-harm or suicide. Thus, two major child and adolescent health issues are highlighted and must be urgently addressed: first, whether there is a treatment strategy that can bridge the gap between the initiation of SSRIs and observed (possibly also additional) clinical benefits, and second, the need to investigate the predictors of response to SSRI treatment, which in turn could save significant time allocated to treatments with little or no effect.

Strong biological and recent clinical evidence has suggested that nitrous oxide (N_2_O) has significant antidepressant effects in adults, in particular in patients with treatment-resistant depression (TRD) [3]. The underlying mechanism of action of N_2_O is thought to be through the *N*-methyl-d-aspartate (NMDA) receptor, because N_2_O serves as an antagonist of this particular receptor [4–6]. Numerous animal studies and human trials have investigated the use of NMDA antagonists in targeting behaviours or symptoms that may be associated with depression. For example, in murine models, the administration of ketamine, which, like N_2_O, is an NMDA antagonist and anaesthetic, showed a reduction in depression-like behaviour, such as increased mobility in the forced-swim test, shorter latencies in the novelty-suppressed feeding test and a reduction in learnt helplessness [7, 8]. In this context, authors of a recent systematic review of studies investigating the use of ketamine to treat TRD in humans suggested it to be associated with a rapid onset of antidepressant effects [9]. Similarly, in a trial where inhaled N_2_O was administered in adults with TRD, Nagele et al. [3], found a significant improvement in depressive symptoms as rated by the 21-item Hamilton Depression Rating Scale (HDRS) at 2 and 24 h and 1 week (in a subset of participants) following administration. These findings are significant because in the underlying neurobiology of depression, the NMDA receptor is thought to play a decisive role [8, 10, 11]. NMDA antagonists, such as N_2_O and ketamine, work by blocking the NMDA receptor, which inhibits a further inhibiting interneuron (GABAergic), resulting in a release of glutamate. Whilst the blocking of the NMDA receptor leads to this sequential effect which impacts three neurons, it has been hypothesised that the blocking of the NMDA receptor leads primarily to an almost immediate antidepressant effect [12–15]. The mechanism of action of SSRIs differs from that of the NMDA antagonists, because it may take a period of weeks following administration before the desensitisation of central nervous system 5-HT receptors occurs, which has been hypothesised to lead to an increase of 5-HT within the synaptic cleft (i.e., antidepressant effect). Therefore, the use of N_2_O, a safe inhalational anaesthetic, has the potential to be a novel, fast-acting and non-intrusive treatment strategy for patients with severe depressive disorders while awaiting onset of SSRI antidepressant activity. Furthermore, in the hospital setting, N_2_O has been used for several decades with an excellent record with regard to safety and effectiveness.

Whilst the described mechanisms of action in depression of NMDA antagonists and SSRIs are not fully understood, animal models have shown that the administration of NMDA antagonists is associated with changes in specific brain areas which are also related to mood, such as the hippocampus and the prefrontal cortex [16]. Most notably, such areas are also highly 5-HT-modulated areas of the brain [4, 17]. Given the significant overlap in neurocircuits, an increase in brain function in terms of improved top-down control in mood-related neurocircuits may be used to explain any possible additive treatment effects of the administration of both N_2_O and SSRIs (e.g., fluoxetine), as well as for investigating N_2_O as a potential predictor of SSRI response. Whilst the significant antidepressant effects of N_2_O in a cohort of adults with TRD has been shown [3], such research questions have never been investigated in minors.

### Study objectives and hypotheses

The objectives and hypotheses of the present study are threefold:
*To investigate the antidepressant effects of 1-h administration of inhaled N*
_*2*_
*O at 24 h post-administration compared with placebo (phase A of the study)*: We hypothesise that a single inhaled administration of N_2_O will lead to a reduction of depressive symptoms in young people with depression compared with a placebo group. Depressive symptoms will be measured through the use of the Beck Depression Inventory (BDI), the HDRS, and the Children’s Depression Rating Scale–Revised (CDRS-R).
*To explore whether a single administration of N*
_*2*_
*O provides any additional improvement in mood when followed by open-label SSRI administration (phase B of the study) over and above the benefits from SSRI administration alone*: We hypothesise that participants treated with N_2_O will show greater improvements in mood (as indicated by change in BDI, HDRS and CDRS-R scores), owing to possible additive effects and possibly faster symptom remission, after 6 and 12 weeks into open-label fluoxetine treatment (phase B of the study) compared with the placebo group.
*To explore whether antidepressant effects (as indicated by changes in BDI, HDRS and CDRS-R scores) associated with a single administration of N*
_*2*_
*O can act as a predictor of SSRI response*: Given the potential overlap in neurocircuits that are associated with the administration of NMDA antagonists and 5-HT, we hypothesise that the use of N_2_O may predict response to the use of the SSRI fluoxetine as a pharmacological treatment.

## Methods/design

### Trial design

The present study will employ a randomised, placebo-controlled, blinded clinical pilot trial design for phase A (N_2_O or placebo), followed by an open-label design using fluoxetine administration in phase B of the study.

### Setting of the study

The present study will be conducted at Princess Margaret Hospital (PMH), Perth, Australia, and is expected to be transferred to the new Perth Children’s Hospital once opened.

### Consent

Written informed consent will be obtained from participants and their parents/guardians by the study psychiatrists at a baseline session. Once consent has been obtained, the study team will arrange thyroid function tests and electrocardiography for each participant to ensure that fluoxetine is a suitable medication for the individual participant to take during phase B of the study.

### Subjects and eligibility criteria

In this study, we aim to recruit a total of 30 participants. There are three key inclusion criteria. First, participants must have a confirmed diagnosis of moderate to severe major depressive disorder according to the International Classification of Diseases, Tenth Revision, or the *Diagnostic and Statistical Manual of Mental Disorders, Fifth Edition*, criteria, with the diagnosis to be confirmed through the administration of the Kiddie Schedule for Affective Disorders and Schizophrenia (K-SADS) [18] as well as a full psychiatric assessment. Second, participants must be aged between 12 and 17 years. Third, participants and their parents/guardians must agree to start fluoxetine as treatment in phase B of the study. Exclusion criteria include any active suicidal ideation or plans, current use of other psychiatric medications at study entry, IQ < 85 (screened using the Wechsler Abbreviated Scale of Intelligence [WASI-II] [19]), active or past diagnosis of an eating disorder, current or recent (i.e., past 12 months) abuse or dependence on alcohol or illicit substances, current pregnancy in female participants, significant chronic medical or neurological disorder, history of bipolar disorder, schizophrenia, schizoaffective disorder, obsessive compulsive disorder or personality disorders, presence of an acute medical illness that could interfere with study participation, active psychotic symptoms, administration of NMDA receptor antagonists during the preceding 3 months, ongoing or past treatment with electroconvulsive therapy, contraindications against the use of N_2_O and contraindications against the use of fluoxetine.

### Intervention

The entire study period will be approximately 14 weeks, including a baseline screening session, followed by phase A and phase B of the study. Specifically, phase A indicates the period in which participants will receive the N_2_O or placebo administration, and phase B refers to the 12-week follow-up period, in which participants’ mood and fluoxetine levels (fluoxetine will be administered using an open-label approach in phase B) will be monitored. All participants will required to participate in both phases A and B. Figure 1 provides a schematic illustration of the procedural flow of the study and the assessments that will be conducted in each phase.

**Fig. 1 Fig1:**
[figure not shown]
An illustration of the medical, biochemical, and psychological assessments that will be conducted during the Nitrous oxide and subsequent open-label SSRI treatment of adolescents with depression (NOTAD) study. *ECG* Electrocardiography, *BDI* Beck Depression Inventory, *CBCL* Child Behaviour Checklist, *CDRS-R* Children’s Depression Rating Scale–Revised, *CGI* Clinical Global Impression, *HDRS* Hamilton Depression Rating Scale, *K-SADS* Kiddie Schedule for Affective Disorders and Schizophrenia, *N*
_*2*_
*O* Nitrous oxide, *WASI-II* Wechsler Abbreviated Scale of Intelligence, *YSR* Youth Self Report

#### Baseline screening

All participants who are referred to this study will be screened at baseline for eligibility to participate. This baseline screening session will consist of a medical review during which a thorough physical and mental health history will be taken. Additionally, participants will undergo a psychiatric review, as well as K-SADS and WASI-II for diagnostic confirmation and to determine IQ, respectively. Written consent will also be obtained during this session.

#### Phase A

On the study day, participants will be assessed by a study psychiatrist for a mental state and risk assessment. Participants will also be required to complete urine pregnancy (females) and drug screens as well as baseline mood measurements (CDRS-R, HDRS, BDI, Child Behaviour Checklist [CBCL] and Youth Self Report [YSR]). Randomisation will occur at this phase. Upon completion of all measures, the participant will be transferred to the theatre complex for N_2_O or placebo administration.

All participants will be asked to fast for 2 h for solids and fluids prior to the administration of N_2_O/placebo, as well as to adhere to routine fasting guidelines for N_2_O administration of the Department of Anaesthesia, PMH. Small sips of water will be allowed up until 30 minutes prior to the intervention. Even though N_2_O administration is standard in many dental practices and obstetrics and general ward settings, for the purposes of this study, the administration of N_2_O will be performed in the theatre complex of PMH, which allows for rapid access to emergency personnel from the theatre in the very unlikely event of complications. N_2_O or placebo will be administered by a qualified nurse or doctor via standard anaesthesia workstations using a standard anaesthesia face mask. A parent/legal guardian or a family member over the age of 18 years may accompany the patient at the theatre complex for the administration of the study treatment. The patient as well as the patient’s parent/guardian will be blinded to the group allocation.

Subjects will be randomly allocated to receive either N_2_O (50% N_2_O and 50% O_2_) or placebo (50% nitrogen/50% oxygen) over a period of 1 h in a blinded fashion. The 50% concentration of N_2_O is based on recent evidence obtained in clinical trials and is also in line with standard N_2_O treatment in the ward and clinic setting outside the operating room [3]. In line with research conducted in adults, an equal concentration of O_2_ will be used to allow adequate comparison and to minimise variability between the two conditions. A standard anaesthesia face mask for this age group will be used for treatment administration. The mask used will be connected to a standard scavenged anaesthesia machine. The total gas flow will be set at 6 L/minute, which is in line with previous research [3]. Enrolled participants will be subject to monitoring during and after treatment administration in accordance with the Australian and New Zealand College of Anaesthetists and PMH guidelines for sedation. Obtained safety data will comprise a continuous three-lead electrocardiogram, pulse oximetry, and non-invasive blood pressure and end-tidal carbon dioxide monitoring. Upon conclusion of the treatment session, subjects will be monitored for a minimum of 30 minutes and returned to the interview area. Participants will then undergo a standardised psychiatric assessment that will include an examination of mental state and risk, as well as the development of a comprehensive management plan prior to discharge.

#### Psychological assessments that will be conducted in phase A

As outlined in Fig. 1, a number of psychological assessments will be conducted in phase A, immediately pre-intervention and 2 h and 24 h after N_2_O or placebo administration. These include the BDI, HDRS, and CDRS-R. The CBCL, YSR and Clinical Global Impression (CGI) will be completed immediately pre-intervention.

#### Phase B

Phase B will start approximately 24 h after N_2_O/placebo administration, and SSRI treatment with fluoxetine (pharmacological treatment as usual [TAU]) will be initiated by the study psychiatrists. The SSRI fluoxetine will be initiated at a starting dose of 10 mg daily for 1 week and titrated up to 20 mg daily in terms of a fixed-dose open-label approach. This is in accordance with the National Institute for Health and Care Excellence clinical guideline for the treatment of depression in children and young people [20]. Fluoxetine will be continued with weekly monitoring of clinical symptoms and mood.

#### Biochemical and psychological assessments that will be conducted in phase B

Blood samples will be taken during weeks 4, 8 and 12 of phase B. These blood samples will be used to assess compliance with the fluoxetine treatment. These samples will contribute to the investigation of the relationship between mood changes and the data relating to N_2_O/placebo administration. Compliance with fluoxetine treatment will also be monitored through empty packet return and patient report. Blood samples will undergo basic laboratory processing before storage in a lockable −80 °C freezer.

Psychological assessments will be conducted on a weekly basis and will include the BDI, HDRS and CDRS. The CBCL, YSR and CGI will be completed during the weeks 6 and 12 follow-up. Measures obtained from the CBCL and the YSR during the weeks 6 and 12 follow-up will be used for additional clinical monitoring purposes. Participants are also permitted to continue their normal mental health TAU, which may include engagement in cognitive behavioural therapy or other forms of psychotherapy for depression. As per recommendation by the local ethics committee, the study does not either prescribe or restrict participation in psychological therapy. This is at the discretion of the participants and their treating clinicians. The type of psychological therapy and number of sessions over the study period will be recorded for each participant on the basis of a report from the participant’s treating clinician. Access to other treatment strategies will be accounted for in the statistical analysis of the data and will be reported upon completion of the study.

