### Outcomes

The primary endpoint for the first aim of the study (to investigate the therapeutic effects of the administration of N_2_O as a single-dose inhalational anaesthetic, phase A) is the assessment of mood symptoms approximately 24 h after administration. Mood symptoms will be measured using psychometric instruments, including the BDI, HDRS and CDRS-R. Further endpoints will be mood changes after 6 weeks (secondary endpoint) and 12 weeks (tertiary endpoint). For the second and third aims of the study (to determine whether the additive effects of N_2_O and SSRI administration provide a clinically significant improvement in mood over and above the benefits from SSRI administration alone [Phase B] and to investigate N_2_O as a possible predictor of SSRI treatment response, respectively), the endpoints will be measurements of mood (indicated by the BDI, HDRS and CDRS-R) at the weeks 6 and 12 follow-up.

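### If therapy sessions received after randomisation enter the week 6 and 12 comparison as covariates, it no longer estimates the total effect of randomised N2O and can be biased

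*Protocol article*

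**What the plan says.** The section on biochemical and psychological assessments in phase B sets out how other care is handled:

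- Usual care may go on: "Participants are also permitted to continue their normal mental health TAU".
- Therapy is left free in both arms: "the study does not either prescribe or restrict participation in psychological therapy". On who decides, the text adds: "This is at the discretion of the participants and their treating clinicians".
- It is measured across the trial: "The type of psychological therapy and number of sessions over the study period will be recorded for each participant".
- It is then used: "Access to other treatment strategies will be accounted for in the statistical analysis of the data". The same sentence promises, as a separate item, to report it once the study is complete.

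On timing, the Phase A section says of the day on which the gas is given: "Randomisation will occur at this phase". The Phase B section starts fluoxetine about 24 h later. For aims 2 and 3, the Outcomes section states that "the endpoints will be measurements of mood (indicated by the BDI, HDRS and CDRS-R) at the weeks 6 and 12 follow-up".

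The section on data preparation and statistical analysis gives a mixed effects linear model for the HDRS and names no covariates. Nothing there, or in the phase B section, limits the accounting to therapy already under way at entry.

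**The concern.** Aim 2 asks whether N2O followed by fluoxetine does better at weeks 6 and 12 than fluoxetine alone. Randomisation is what makes the two groups comparable for that question. A session count built up over the following 12 weeks is not a baseline characteristic. The trial's own hypothesis is that N2O improves mood within 24 h and leaves patients better at weeks 6 and 12. If that is true, and if patients who stay unwell are offered or seek more therapy, the session count is partly a result of the treatment.

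Putting such a variable in the model does two things. It takes out whatever part of the N2O effect runs through therapy uptake. It also compares N2O and placebo patients with the same number of sessions, who need no longer be alike in underlying severity. At stake is the interpretation of the aim 2 result: a promise meant to make the comparison fairer could make it less so.

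**Working it through.** **Inputs.** From the article: randomisation on the phase A day, phase B from about 24 h, discretionary therapy, sessions counted over the study, endpoints at weeks 6 and 12, at most 15 participants per arm. The article gives no figure for the phase B effect, for therapy uptake, or for its relation to mood, so there is no stated figure to reproduce. Every coefficient below is an assumption.

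**General form.** Let D be the effect of arm on sessions, and b the within-arm slope of the week-12 score on sessions. In a linear model

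adjusted effect = total effect − b × D.

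There is no bias when D = 0. That holds if N2O has no effect, or if uptake depends on neither arm nor mood. If N2O reduces sessions (D < 0), the sign of b sets the direction. When b is positive, because sicker patients have more sessions, the estimate moves towards the null. When b is negative, because the benefit of therapy dominates, it moves away.

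**Illustration 1, closed form.** Suppose sessions correlate c with early mood within arm, early mood correlates ρ with the week-12 score, and therapy itself has no effect. In SD units b = ρc and D = c × (early effect), so the amount removed is ρc² × (early effect). If the early and week-12 effects are also equal, the proportional loss is ρc²:

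- ρ = 0.5, c = 0.5: 0.5 × 0.25 = 12.5%
- ρ = 0.7, c = 0.5: 0.7 × 0.25 = 17.5%
- ρ = 0.5, c = 0.7: 0.5 × 0.49 = 24.5%
- ρ = 0.7, c = 0.7: 0.7 × 0.49 = 34.3%

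A true effect of 0.50 SD in the first case becomes 0.50 × 0.875 = 0.4375; large simulations gave 0.437. The result leans on the equal-effects assumption. If N2O acts on week 12 only through early mood, the week-12 effect is ρ times the early effect and the loss is c², that is 25% to 49%.

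**Illustration 2, simulation in which therapy can work.** 15 per arm, 20,000 runs per case. A is arm, U is latent severity, and each e is independent standard normal noise; higher scores are worse.

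- Early mood M = −0.5A + 0.7U + 0.7e
- Sessions S = aM + uU + e
- Week-12 score Y = −0.3A + 0.5M + 0.5U − sS + 0.6e (SD about 1)
- Total effect = −0.3 − 0.5 × 0.5 + s × a × 0.5; in the null case both N2O effects are set to 0

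| Case (a, u, s) | True | Unadjusted | Adjusted | Shift from true |
|---|---|---|---|---|
| N2O has no effect (0.5, 0.3, 0.3) | 0 | −0.002 | −0.002 | none; type I error 0.049 vs 0.050 |
| Uptake unrelated to mood (0, 0, 0.3) | −0.55 | −0.547 | −0.546 | none |
| Weak dependence (0.25, 0, 0.3) | −0.513 | −0.511 | −0.524 | about 2% away from null |
| Moderate (0.5, 0.3, 0.3) | −0.475 | −0.473 | −0.436 | about 8% towards null |
| Strong (1, 0.3, 0.3) | −0.40 | −0.402 | −0.332 | about 17% towards null |
| Moderate, therapy without effect (0.5, 0.3, 0) | −0.55 | −0.546 | −0.438 | about 20% towards null |

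**Check of the change of sign by the general form.** Within arm, var(M) = 0.49 + 0.49 = 0.98 and cov(M, U) = 0.7.

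- Weak: var(S) = 0.0625 × 0.98 + 1 = 1.061. b = 0.5 × (0.245 + 0.175)/1.061 − 0.3 = −0.102. D = −0.5 × 0.25 = −0.125. Adjusted = −0.5125 − (−0.102)(−0.125) = −0.525.
- Strong: var(S) = 0.98 + 0.09 + 0.42 + 1 = 2.49. b = 0.5 × (1.19 + 1.00)/2.49 − 0.3 = 0.140. D = −0.5. Adjusted = −0.40 − (0.140)(−0.5) = −0.330.

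Both agree with the simulation. One extra covariate costs almost no power by itself: rejection rates were 0.245 and 0.249 where uptake was unrelated to mood. The problem is what is being estimated, rather than the degree of freedom.

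**The case against.** A reader might infer that the plan adjusts for follow-up therapy and that its phase B result is therefore biased. The article does not support that.

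- No method, model or endpoint is named. The promise could be met by a table by arm, a sensitivity analysis or a covariate, and such detail is ordinarily left to a full protocol or analysis plan that is not shown.
- The article nowhere says that uptake follows mood. It says only that the decision is discretionary, and some therapy may have begun before entry and so be a baseline characteristic.
- Bias needs uptake to depend on arm, or on mood changed by arm. In the simulations it vanished without either, and in one case it ran away from the null.
- The 12%–34% range further assumes equal early and week-12 effects and ineffective therapy.
- The primary endpoint falls at about 24 h, before nearly all phase B sessions. Aim 2 is exploratory, in a pilot of 30.

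All of this stands, and it limits the claim to a conditional one. It does not dispose of the point. The sentence promises reporting separately, so accounting for therapy in the statistical analysis most naturally means something beyond a descriptive table. The only data named for it are type and sessions over the whole study. The point therefore concerns a stated commitment whose natural execution is unsafe for aim 2. It does not complain of a missing detail.

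**Conclusion.** The point holds in conditional form. The article commits to using largely post-randomisation, discretionary therapy data in the analysis and does not restrict this to baseline status. If those data enter the week 6 and 12 comparison as covariates, the estimate is no longer the total effect of randomised N2O. It can then be biased whenever uptake depends on arm or on mood changed by arm.

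Size and direction cannot be known from the document. The illustrations span about 2% away from the null to roughly 12%–34% towards it. All rest on assumed coefficients, and the range is not a bound. The distortion is nil if N2O has no effect or if uptake is unrelated to mood. The 24 h primary endpoint is essentially unaffected. The point is worth correcting because the safe wording is specific and nearly free.

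**What to change.** Replace the general promise with wording such as: *The week 6 and week 12 comparisons are made by randomised arm and are not adjusted for therapy received after randomisation. Only therapy status recorded before randomisation may enter as a covariate. Type and number of sessions are reported by arm. Any model that includes sessions received after randomisation is exploratory and is not given a causal interpretation.*

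The cost is this short statement and, if current therapy is not already captured in the history taken at screening, one baseline item. Session recording stays as planned.
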